### Dropout criteria

Occurrence of severe cardiovascular and cerebrovascular disease or complications which result in stopping the trial;Patients who have severe adverse reactions after acupuncture and cannot successfully complete the course of treatment;The participant was unable to follow the protocol treatment for personal reasons during the course, or reject to continue the study.

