### MC group

Patients randomized to the MC group will be given aspirin enteric-coated tablets (100 mg qd po, Bayer) and atorvastatin calcium tablets (10 mg qd po, Pfizer) for antiplatelet aggregation as well as lipid-lowering effects. The drugs will be administered and provided to patients for free every week by the researchers. Once the patients forget to take pills or stop for personal reasons, researchers will record the detailed to individual situations. If patients are required to take other drugs for a long period due to illness, then the drug name, dosage, and frequency will be recorded.

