### Safety assessment

To reduce the risk of adverse events, firstly, acupuncturists should have years of work experience. Before the study begins, all acupuncturists need a unified training to standardize the acupuncture operation and increase the safety of acupuncture. Secondly, during the research process, the cardio-cerebrovascular doctor will evaluate the patient’s condition to ensure that the patients with severe cardio-cerebrovascular disease during the study period can be treated in time. During the treatment, the acupuncturist will also evaluate the subject’s condition to reduce the occurrence of adverse events. Finally, this study will be conducted in Guangdong Provincial Hospital of Traditional Chinese Medicine. The hospital has a strong medical level and ability to handle crisis events, which can guarantee the progress of this study. Acupuncture may cause some adverse reactions, such as bleeding, redness, fainting, and pain. All adverse events need to be recorded in common reporting format (CRF) tables. Adverse event records should include time, symptoms, extent, and their relationship with acupuncture. The investigator should handle and record adverse events. Serious adverse events should be reported to the Guangdong Provincial Hospital Ethics Committee. Participants who are unable to continue participating in the study due to adverse events will be excluded.

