### Data collection and management

This study will collect population data from eligible participants before the first treatment; these data include name, age, duration, occupation, blood pressure, sex, and body mass index (BMI). Drug and acupuncture adverse reactions will be recorded during the treatment and follow-up periods based on the reaction of the participants. At weeks 0, 12, and 24, data on carotid ultrasound, blood lipids, platelet aggregation, fibrinogen, platelet count, and apolipoprotein A-IV will be collected. The data collection will be performed by three staff members who will not take part in acupuncture treatment, index evaluation, statistical analysis, or grouping. The data collection and entry will be performed independently by two of the staff members and finalized by a third staff member. The main investigators, acupuncturist, sonographers, and laboratory staff will not be involved in data collection.

All data must be saved in paper with identification codes in seal, while electronic data is saved on the ResMan Research Manager of the Clinical Trial Management Public Platform, and photo formats are also named with identification codes to ensure authenticity and integrity. All data must be saved in paper, electronic, and photo formats to ensure authenticity and integrity. The data should be kept for at least 5 years after the article is published. A data monitoring committee was also set up in this study, composed of experts with good clinical research experience in the Department of Acupuncture of Guangdong Provincial Hospital of Traditional Chinese Medicine. Experts will regularly monitor research progress, data, participant management, distribution, and more. The committee is independent from the fund sponsor and has no conflicts of interest. Researchers who take charge in the data collection and entry will have access to the interim results and report to main investigators if necessary. Consequently, the main investigators will make the final decision to terminate the trial after discussion.

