### Statistical analysis

This study will use per-protocol (PP) and intention-to-treat (ITT) analysis principles. ITT will include all subjects who participated in at least one treatment, including participants who dropped out. Missing data for participants who dropped out will be supplemented with the most recent data. The PP principle will analyse all participants’ data that conform to the study protocol, and those of individuals who did not conform to the protocol will not be included.

The data will be analysed by professional statisticians with SPSS 20.0 software (IBM SPSS Statistics, IBM Corp, Somers, NY, USA). First, we will describe the baseline data, such as age, blood pressure, course of the disease, BMI, and sex, and compare the baseline data between the three groups. The continuous variables will be presented as the mean ± standard deviation (SD), and the categorical variables will be presented as the composition ratio and rate.

Continuous variables that conform to a normal distribution will be analysed by ANOVA, and the non-conforming data will be analysed using the rank sum test. Categorical variables will be analysed using the chi-square (*χ*^2^) test or Fisher’s exact test. The confidence interval (CI) will be estimated at 95%, and the significance level will be set at 0.05. A *P* value < 0.05 will be considered statistically significant. The adverse data will be recorded and analysed for the relationship with acupuncture. We will calculate the dropout rate and analyse the reasons for dropping out.

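### The stated causality assessment and adverse event analysis refer to acupuncture alone, so they are uninformative for the arm that receives aspirin and atorvastatin

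*Protocol article*

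**What the plan says.** All references are to the protocol article.

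- **Safety assessment** sets a broad scope for capture: "All adverse events need to be recorded in common reporting format (CRF) tables". The next sentence fixes the content: "Adverse event records should include time, symptoms, extent, and their relationship with acupuncture". The only expected reactions listed are those of needling: "Acupuncture may cause some adverse reactions, such as bleeding, redness, fainting, and pain". The section ends by saying that participants who cannot continue because of adverse events are excluded, without limiting the cause.
- **Statistical analysis** gives adverse data a sentence of its own: "The adverse data will be recorded and analysed for the relationship with acupuncture". A general chi-square or Fisher rule for categorical variables stands earlier in the section and is not tied to adverse events.
- **Data collection and management** is wider: "Drug and acupuncture adverse reactions will be recorded during the treatment and follow-up periods based on the reaction of the participants".
- **MC group** describes a pure drug arm: "Patients randomized to the MC group will be given aspirin enteric-coated tablets", together with atorvastatin. The Intervention section bars other acupuncture during the study.
- **Dropout criteria** name, among other reasons, "Patients who have severe adverse reactions after acupuncture and cannot successfully complete the course of treatment". No matching item names drug reactions.

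**The concern.** One of the three arms is treated with two drugs, and the protocol expects drug reactions to be recorded. Yet the two places that say how events are to be attributed and analysed name acupuncture only. Asking whether an event is related to acupuncture tells us nothing about a participant who had none.

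This matters because drug side effects are part of the argument for the trial. The Background cites gastrointestinal irritation and bleeding with antiplatelet drugs and muscle effects with statins. The Discussion says that side effects of drugs remain hard to avoid. A reader of the results will want to know how many treatment-related events occurred under acupuncture and how many under medication. The attribution as worded cannot answer that, and this pilot is meant to guide larger trials.

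**Working it through.** **1. Size of the arm affected.** The Sample size section takes 30 per group and about 15% dropout. 30 × 1.15 = 34.5, rounded up to 35, and 3 × 35 = 105, which matches the plan. (Dividing instead, 30 / 0.85 = 35.3, would give 36 per group and 108 in total; nothing here depends on that.) The MC share is 35 / 105 = 33.3%.

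**2. What the stated attribution can show in each arm.**

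| Arm | Receives | What a rating against acupuncture can show |
|---|---|---|
| TA | Needling | Related or unrelated to the assigned treatment |
| SA | Non-penetrating blunt needle at the same points | Interpretable only if the sham procedure is read as acupuncture |
| MC | Aspirin and atorvastatin | Always unrelated, whatever the event |

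If x of the 35 MC participants have an event caused by a study drug, the number rated as related to acupuncture is 0 for every x from 0 to 35. The MC count on the stated attribution is therefore fixed by design and is not an observation.

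**3. One event type in two arms.** Bleeding is listed in Safety assessment as a reaction to acupuncture and in the Background as an effect of antiplatelet drugs. In TA a bleed can be rated as related. In MC the same event can only be rated as unrelated to acupuncture. A comparison of related bleeds between TA and MC would set an observed count against a structural zero. That asymmetry could make acupuncture look worse than medication, so the wording does not even reliably favour the treatment under test.

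**4. What is not lost.** Every adverse event goes into the CRF tables with time, symptoms and extent. The randomised arm is known. Incidence by arm can therefore be computed without any causality field.

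**5. The places that do not fit together.**

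- Data collection and management presupposes that a drug reaction can be recognised as such. Safety assessment and Statistical analysis provide no field and no analysis for it.
- The Dropout criteria tie the adverse reaction item to acupuncture, while Safety assessment removes anyone unable to continue because of any adverse event. An MC participant who stops for a drug reaction is covered by the second and has no clear category under the first. Statistical analysis plans to analyse reasons for dropping out, so the mismatch would reach a reported result.

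**The case against.** Several points on the other side are sound.

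- **Capture is complete.** A reader might infer that events in the drug arm go unrecorded, or that events are classified solely by their link to acupuncture. The documents do not support that: all adverse events are captured, and drug reactions are recorded over treatment and follow-up, which implies some attribution to the drug.
- **No between-arm safety comparison is specified.** The Study design section sets MC as a positive control for curative effect. Calling the safety comparison one-sided would be an inference about an analysis that the article does not describe. Counts by arm remain open.
- **The inconsistency is narrow.** It lies between Safety assessment and Statistical analysis on one side and Data collection and management on the other, with a separate wording mismatch in the Dropout criteria. The MC group section only describes the drugs and contradicts nothing. Withdrawal for any adverse event is covered in Safety assessment.
- **A projected number of missed events is not available.** It is tempting to apply the Background's 7–29% for statin-related myositis to the 35 MC participants. That figure comes from a survey quoted without dose or duration, and the Discussion reports fewer side effects at the atorvastatin dose used. It would also count possible events without measuring any bias from the wording.
- **A fuller plan may exist.** Safety tables are often left to an analysis plan, and the record content is worded as something that should be included, which can be read as a minimum.

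The last point does not dispose of the matter. The article is not silent: it names a relationship to be recorded and analysed, twice, and both times it is acupuncture. An unseen plan could add detail, but the published rule would still not fit a third of the participants. The general test for categorical variables does not repair it either, since a test by arm on this attribution would meet the same structural zero in MC.

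**Conclusion.** The point holds in a limited form. The stated causality assessment and the stated adverse event analysis are confined to acupuncture, although 35 of 105 participants (33%) receive drugs and no acupuncture, and the article itself says that drug reactions are recorded. The attribution analysis is uninformative for MC and cannot support an attribution-based comparison of TA with MC. Crude incidence by arm is unaffected and can still be reported.

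This rests on the wording of the article alone and assumes that the causality field is used as described. It does not depend on any assumed rate of drug reactions, and no number of misclassified events is claimed. The efficacy outcomes are not touched. It is a badly fixed rule that should be corrected, not a threat to the trial's main results.

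**What to change.** 1. In Safety assessment and in Statistical analysis, have the relationship refer to the assigned study intervention in place of acupuncture, so that it can be rated in TA, SA and MC alike and agrees with Data collection and management.
2. State that all adverse events and serious adverse events will be summarised by randomised arm whatever the causality rating. This table should carry the safety comparison: drug treatment cannot be disguised as needling, so attribution in MC is made with the treatment known, whereas arm counts need no such judgement.
3. Reconcile the Dropout criteria, which tie severe reactions to acupuncture, with Safety assessment, which speaks of inability to continue because of any adverse event. The two need to agree; which rule applies is for the investigators to decide.

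The cost is one CRF field, one table and a change of wording, with no extra visits or participants. Events already recorded would need attribution in retrospect. The Trial status section reports 42 participants by October 2019, so the task covers any events in those participants and in those recruited since, and attributions added in this way should be marked as retrospective.

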### Sample size

This is a three-arm study. In our search for previous studies of the effects of acupuncture on the carotid atherosclerotic plaque, it was found that most of the studies were two-arm studies of acupuncture versus drugs. There is a lack of high-quality clinical research. In addition, the effect of acupuncture exhibits a significant correlation between acupoints. Therefore, it is not appropriate to use the previous acupuncture clinical research literature data to estimate the sample size. Furthermore, this is a pilot study to guide future randomized controlled trials and to test the feasibility of the protocol. Considering that there are many clinical blood tests in the study, we will choose the clinical minimum sample size of 30 individuals for each group to reduce the burden of detection of the subjects. The maximum dropout rate within the intervention is expected to be approximately 15%. The total number of patients needed to be randomized is therefore 105 (35 for each group).

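### The fate of participants who stop because of an adverse event is left unclear, and the set called ITT is not all randomised participants

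*Protocol article*

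**What the plan says.** Three sections of the protocol article bear on a participant who stops because of an adverse event.

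- **Safety assessment**, closing sentence: "Participants who are unable to continue participating in the study due to adverse events will be excluded". The sentence names no object: treatment, study or analysis.
- **Dropout criteria**: one listed category is "Patients who have severe adverse reactions after acupuncture and cannot successfully complete the course of treatment". The others are severe cardiovascular or cerebrovascular disease or complications that stop the trial, and personal reasons or refusal.
- **Statistical analysis**: "ITT will include all subjects who participated in at least one treatment, including participants who dropped out". Gaps are filled by a carry-forward rule: "Missing data for participants who dropped out will be supplemented with the most recent data". For the per-protocol set, "those of individuals who did not conform to the protocol will not be included".

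The Primary outcome section schedules plaque volume (PV) and grey-scale median (GSM) at weeks 0, 12 and 24 only. Treatment runs for the first 12 weeks.

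**The concern.** An analyst must know which participants enter the comparison and with which values. Here one section excludes a participant whom another section appears to keep. Whether someone stops for an adverse event is known only after randomisation and may depend on the arm, so removing such people would mean comparing groups other than those randomised.

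Reading the sentence as withdrawal from the study avoids that conflict but creates another problem. The article then relies on carry-forward for people who could have been measured at visits already in the schedule.

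The third element needs no interpretation. A set that requires at least one treatment leaves out anyone randomised but never treated. Participants allocated to aspirin and atorvastatin know that they are not being needled, and the blinding questions are put only to the acupuncture (TA) and sham (SA) groups. Loss between allocation and first treatment could therefore differ between the medication group (MC) and the other two.

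**Working it through.** **1. The plan's own figure.** The Sample size section states "we will choose the clinical minimum sample size of 30 individuals for each group" and "The maximum dropout rate within the intervention is expected to be approximately 15" per cent, giving 35 per group and 105 in total.

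- 30 × 1.15 = 34.5, rounded up to 35; 3 × 35 = 105. This reproduces the stated figure.
- 30 / 0.85 = 35.29, rounded up to 36. The two conventions differ by one patient per group, which is immaterial here.
- Losing 15% of 35 leaves 35 × 0.85 = 29.75 per group.

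**2. The two readings side by side.**

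| Reading of *excluded* | Fit with Dropout criteria and Statistical analysis | Consequence |
|---|---|---|
| Removed from the analysis | Conflicts: stoppers with severe acupuncture reactions are dropouts, and dropouts with at least one treatment stay in ITT | An ITT set without its adverse-event stoppers |
| Withdrawn from the study | Consistent | No week-12 or week-24 measurement; earlier values are carried forward |

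The Dropout criteria name reactions after acupuncture but not drug reactions. Whether an MC participant stopped by a drug reaction counts as a dropout under the ITT sentence is thus less plain.

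**3. What carry-forward does on the second reading.** For a participant who leaves during treatment, the latest PV or GSM is the week-0 value. The analysed change is baseline − baseline = 0 at both week 12 and week 24. If a fraction f of an arm is handled this way and their true mean change would have been c, the arm's mean change is wrong by f × c. The article gives neither f nor c.

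**4. How many participants could be involved.** The 15% covers dropout for all causes and the adverse-event share is not stated. Under assumed shares:

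| Assumed adverse-event share of dropout | Fraction of arm | Participants out of 35 | Remaining if removed |
|---|---|---|---|
| 25% | 0.0375 | 1.3 | 33.7 |
| 50% | 0.075 | 2.6 | 32.4 |
| 100% | 0.15 | 5.3 | 29.8 |

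**5. Size of the shift on the first reading.** If a fraction f is removed and its mean differs from the rest of the arm by d SD, the arm mean moves by f × d. Both ranges are assumptions: f from 0.05 to 0.15 (the top being the plan's whole dropout allowance), and d from 0.5 to 1.0.

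- Smallest: 0.05 × 0.5 = 0.025 SD
- Largest: 0.15 × 1.0 = 0.15 SD

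This takes the loss to fall in one arm only; similar losses in the comparator would partly cancel it.

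**6. Yardstick.** With 30 per arm, the 95% confidence half-width for a difference between two means is t(0.975; 58) × √(2/30) = 2.002 × 0.258 = 0.517 SD. The range above is 0.025/0.517 = 5% to 0.15/0.517 = 29% of it.

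**7. Randomised but never treated.** No number is given. Each such participant is 1/35 = 2.9% of an arm, and the ITT definition omits them on any reading.

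**The case against.** The best defence is that only the Statistical analysis section defines analysis sets, and it explicitly keeps dropouts. The carry-forward rule would have little purpose if they were removed. The safety sentence closes a passage on handling harm and can be read simply as withdrawal from further participation, which agrees with the other two sections. This stands, and it rules out a stronger inference: that the plan removes harmed patients from the efficacy comparison, or sets up two rival analysis sets for the primary result. The documents establish neither.

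A reader might also infer that the exclusion favours acupuncture, with needle reactions in TA, drug reactions in MC and few in SA. The article gives no adverse-event rates by arm. It lists bleeding, redness, fainting and pain as possible acupuncture reactions and ties none of them to worse PV or GSM. The direction of bias is therefore not shown.

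The defence can add that this is a pilot without a powered test, and that follow-up detail and the choice of primary set are commonly left to fuller documents. That is fair, and the absence of a named primary set is not part of this point. It does not answer what the article does state: an undefined exclusion, a carry-forward rule that becomes baseline carry-forward for early stoppers, and an ITT definition narrower than all randomised. On the benign reading the safety sentence also adds little, since its subjects are already unable to continue, so a careful analyst could still take it as a rule about the data.

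**Conclusion.** The point holds as a matter of unclear wording with a real consequence on either reading. Read one way, the safety sentence conflicts with the ITT rule; read the other, early stoppers are scored as having zero change in both primary outcomes. The at-least-one-treatment restriction is a separate, unambiguous departure from intention to treat.

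The size of any bias is unknown. The 0.025–0.15 SD range rests wholly on assumed fractions and differences, carries no established sign, and is well inside the sampling error of a comparison of 30 against 30. The carry-forward error and the effect of omitting untreated participants cannot be sized from the article. No stated figure changes. Severity is moderate to minor: it should be corrected before analysis, chiefly because this pilot is meant to guide later trials, but it does not undermine the design.

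**What to change.** Reconcile the three sections as follows.

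- **Safety assessment:** state that exclusion does not mean removal from the analysis. For example: *A participant who stops because of an adverse event is invited to the scheduled week-12 and week-24 assessments unless consent is withdrawn, and is analysed in the randomised arm.*
- **Dropout criteria:** add a cross-reference saying that meeting a criterion does not remove a participant from the ITT set, whichever arm the event occurs in. The criteria themselves need not change, and nothing here bears on when treatment should stop.
- **Statistical analysis:** define ITT as all randomised participants, analysed by allocated arm, whether or not treatment began.

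The cost is a few sentences, notified to the ethics committee and registry as the article already requires for protocol changes, plus attendance at already scheduled visits by at most about five participants per arm (15% of 35). For anyone whose visits have already passed, the missing values cannot be recovered, but the set definitions can still be corrected before analysis.
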